**I. Clinic pre-recruitment**	
A. The primary care physician will determine patient eligibility during the clinical appointment and provide the potential participant with a study fact brochure that describes the study and provides an 800 number for questions. Physicians will share the name and phone number of eligible patients with study staff based on patient permission.	
B. Participating clinical facilities will look through charts daily to identify those patients that met inclusion criteria but were not informed of the study by their provider. A cover letter about the study will then be mailed to these patients under the signature of the provider along with the study fact brochure.	
**II. Telephone recruitment**	
A. Patients who do not opt out in Phase 1 A will receive a telephone call within 24 h from the study staff.	
B. Patients who are identified in Phase 1 B will be provided in the letter with an opt-out number to call if they do not want to be contacted by study staff. Staff will attempt to contact patients that do not call to opt out within 72 h.	
C. Once study staff make telephone contact with the participant on the phone:	
1. Study staff will assess eligibility, review the content of the study fact brochure, and answer questions.	
2. Study staff will seek verbal informed consent and contact information including email address and preference for email versus text.	
3. If a participant prefers to physically sign the informed consent script, two hard copies will be mailed to the participant with a pre-stamped pre-addressed return envelope with instruction to keep one copy and mail back the second signed copy.	

## Assignment of interventions: allocation

### Sequence generation {16a}

Baseline SRQ results will be used to stratify randomization of eligible patients across study arms. This will be done initially using the 3-way cross-classification of depression symptom severity, chronicity, and comorbidity based on a SAS macro that will be run daily by the WVU study data manager until 100 participants are assigned per arm. The finite selection model [46] will be used subsequently to randomly assign patients and balance on a larger set of variables, again with the WVU study data manager implementing the procedure daily.

### Implementation {16c}

Initial stratification by the 3-way cross-classification of depression symptom severity, chronicity, and comorbidity will be implemented by a SAS macro that is independent of the WVU data manager that implements the assignment. The subsequent stratification based on the finite selection model will also be implemented by computer, again independent of the WVU data manager that implements the assignment.

## Assignment of interventions: blinding

### Who will be blinded {17a}

Clinical staff at primary care facilities and telephone recruiters will be blinded at the time of recruitment to treatment assignment, which will take place after recruitment is complete. Telephone interviewers that obtain self-report information from participants who did not complete their SRQ will also be blinded to treatment arm.

### Procedure for unblinding if needed {17b}

If concerning symptomology emerges as defined in the Data Safety and Monitoring plan, the participant will be flagged and reported to the PI for review. If a participant’s SRQ indicates acute serious suicide risk, a closing statement in the SRQ will encourage the participant to contact the National Suicide Prevention Lifeline and will inform the participant that both their treating physician and the National Suicide Prevention Lifeline are being informed of their suicidality.

## Data collection and management

### Plans for assessment and collection of outcomes {18a}

Assessments will be carried out with patient-reported SRQs augmented by EMRs that will provide information about relevant baseline information (e.g., information about treatment history prior to the intervention that might be relevant in predicting outcomes or HTE) as well as treatment information over the course of the trial involving both the ADM (type, dose, titration, switching, augmentation) and other treatments that might be relevant to outcome assignment among patients lost to follow-up in the SRQ assessments (e.g., psychiatric hospitalizations, emergency department visits for mental health crises, suicide attempts, suicide deaths, other deaths by external cause). Additionally, assessments will be gathered via smartphone with consenting participants capturing ecological momentary assessments as well as sensor data from the smartphone app mindLAMP [82, 83] that can be used to derive estimations for daily physical activity, sedentary activity, sleep duration, screen time exposure, and social behaviors. Participants will be asked to download an Apple or Android version of mindLAMP onto their personal smartphones for these measures.

The SRQs will be collected remotely by a health survey firm that has extensive experience implementing mixed-mode web-phone surveys. Computerized procedures will be used to automate skip logic, flag missing values for completion, disallow out-of-range and inconsistent responses, and discourage superficial responses. This survey firm will also carry out the telephone interviews with SRQ nonrespondents. Each SRQ will be sent by email. Reminders to initial nonrespondents will be sent 3 and 6 days later. Options will be provided for participants who want to break up an SRQ for completion over multiple sessions. Telephone follow-up calls and interviews with initial SRQ nonrespondents will be carried out by the survey firm in conjunction with the SRQs at 2, 16, 26, and 52 weeks. The survey firm will also maintain an 800 number for technical assistance.

As noted above, more than two dozen consistently significant baseline patient-reported predictors of MDD HTE have been documented in the literature [33]. These are outlined in Table 5. We developed a baseline self-report SRQ to assess these predictors by carrying out a systematic literature review of the best available short-form patient-reported measures of each construct. We also worked with statisticians and psychometricians to develop optimal short-form scales in secondary analyses to create new short-form versions of existing scales when none already existed [84–86]. We made extensive use of intelligent skip logic in designing the baseline SRQ to shorten the assessment once scale scores in a relevant range could be inferred from partial responses.

**Table 5 Tab5:** Baseline predictors

Baseline constructs	Predictors
Demographics	Age [87], gender [87], educational attainment employment status [87], occupation/industry [88], marital/relationship status [87], number of children [87]
Depression history and features	Depression symptom severity [64, 89]; Melancholic features [90–92]; Mixed features [91, 93, 94]; Anhedonia [95, 96]; Atypical depression [64, 89, 90, 97], Endogenous depression [98–100]; History and persistence [98–100]; Suicidality [101–103]
Other comorbid disorders/symptoms	Anxiety [64, 91, 99]; Panic [99]; Anger [98]; Irritability [64]; Dissociative symptoms [91, 99]; PTSD [104, 105]; Substance use/abuse [87, 106]; Psychotic symptoms (exclusionary); Bipolar disorder (exclusionary); Personality disorders [1, 107, 108]; Other comorbid disorders [98, 109, 110]; Somatization/somatic anxiety [91, 111–114]; Sleep problems [115]; Pain [98, 116, 117]; Role functioning/impairment [118]
Stress and adversity	High current stress [98]; Stressful life events [98, 119, 120]; Childhood trauma and maltreatment [121–124]; Parental bonding [125]; History of Traumatic Brain Injury [98]; Social media use [126]; Social support [99, 127]; Perceived belongingness and burdensomeness [128]; Loneliness [129]; Religiosity [98–130]; Masculinity norms [131–133]
Personality traits and temperament	Alexithymia [134]; Attentional control [135]; Attachment style [136]; Emotional regulation [137]; Self-blame [138]; Positive reappraisal [138]; Coping ability [64]; Life satisfaction [64]; General sense of well-being [64]; Positive sense of mental health [64]; Posttraumatic growth [139]; Perceived self-efficacy/control [140]; Resilience [141–143]; Stress reactivity [144]; Hopelessness [145]; Rumination [146]; Negative affect/neuroticism [84, 147–156]; Emotionality [149, 156]; Openness to experience [84, 98, 157]; Extraversion [84, 147, 148, 152, 153, 158]; Conscientiousness [84, 149, 152, 157]; Mastery [159]; Self-esteem [160]; Problem-solving ability [161]; Cyclothymic temperament [147, 148, 153, 162]; Hyperthymic temperament [147, 148]
Treatment engagement and related constructs	Healthcare utilization [94]; Continuity of care [163]; Health literacy [164]; eHealth literacy [165]; Treatment history [94]; Adherence [166–168]; Therapeutic alliance [169]; Patient-provider communication [170, 171]; Shared decision-making [79]; Patient preferences [172]; Acceptability and willingness [173]; Expected medication side effects [174]; Treatment expectancies [175]
Other	Concentration/decision making [176]

We also noted above that the primary outcome in AMHI will be remission defined by a modified version of the composite RDQ [64] that substitutes the QIDS-SR [71] for the RDQ depression symptom severity scale. Secondary outcomes in addition to the component dimensional RDQ and QIDS-SR scores will include a substance use disorder symptom scale [77], a measure of ADM treatment compliance, measures of patient engagement in treatment based on both self-reports and administrative records [78], and a patient-reported measure of shared decision-making [79], all of which are based on widely-used self-report scales that have good psychometric characteristics as shown in Table 6.

**Table 6 Tab6:** Self-report questionnaire (SRQ) outcomes

	Assessment timepoints							
	2 weeks	4 weeks	8 weeks	13 weeks	16 weeks	26 weeks	39 weeks	52 weeks
**Primary outcome**								
Dichotomous definition of remission from depression^a^					X	X	X	X
**Secondary outcomes**								
Dimensional remission from depression scores^a^					X	X	X	X
Substance use disorder symptoms^b^					X	X	X	X
Treatment compliance^c^	X	X	X	X	X	X	X	X
Treatment engagement^d^	X	X	X	X	X	X	X	X
Shared decision making^e^								X
Perception of recovery/remission^f^	X	X	X	X	X	X	X	X
Treatment satisfaction^f^	X	X	X	X	X	X	X	X
**Other measures**								
Current stressors^g^	X	X	X	X	X	X	X	X
Current treatment^h^	X	X	X	X	X	X	X	X
Medication side effects^i^	X	X	X	X	X	X	X	X

^a^Operationalized with questions from the Remission from Depression Questionnaire (RDQ) [64], 16-Item Quick Inventory of Depressive Symptomatology Self-Report Scale (QIDS-SR) [89], full Inventory of Depressive Symptomatology Self-Report Scale (IDS-SR) [90], Composite International Diagnostic Interview (CIDI) [94], DSM-5 Anxious Distress Specifier and Melancholic Features Specifier for Depressive Disorders [91], and the Sheehan Disability Scale (SDS) [118]

^b^The 7-question PROMIS Alcohol/Substance Use Short Form - 7a scale [87, 106]

^c^Adapted two questions from the Brief Adherence Rating Scale (BARS) [177] to assess medication and psychotherapy treatment compliance [78]

^d^i-CBT engagement will be monitored by analyzing SilverCloud meta-data

^e^The 3-item CollaboRATE scale [79]

^f^Created questions to measure patient perceived remission [178, 179]; and treatment satisfaction [180]

^g^Questions taken from Army STARRS Survey [98]

^h^Items developed for AMHI Study

^i^The Frequency, Intensity, and Burden of Side Effects Ratings (FISBER) scale [174]

### Plans to promote participant retention and complete follow-up {18b}

It will be made clear to participants at the onset of the recruitment process that they will be expected to complete a series of 10 study tasks (baseline SRQ and online challenge tasks to evaluate cognitive performance; and follow-up SRQs at 2, 4, 8, 13, 16, 26, 39, and 52 weeks). We will use a citizen-scientist model to appeal to participants to complete as many of these assessments as possible, emphasizing the special importance of the 16-week and 52-week assessments. Participants will be paid for their time completing all assessments, including $50 for the baseline SRQ and $50 for the cognitive challenge task, $50 for the 52-week SRQ, and $20 for each of the other SRQs. Reminder emails and texts will be used to increase response. In the case of the 2-, 16-, 26-, and 52-week assessments, we will also use telephone reminder calls both to encourage SRQ completion and to collect this information via telephone interview when we cannot do so by SRQ.

### Data management {19}

The WVU study team will maintain a master dataset for all patients who were referred to the project for recruitment along with their dispositions (i.e., withdrew from participation before or after completing the baseline SRQ or after initiating the intervention, were judged ineligible before or after completing the baseline SRQ, were terminated from the study after initiating the intervention, continued throughout the study). Research ID numbers will be assigned separately to this disposition file and to a file containing all personally identifying information (PII) but the PII will not be linked directly to the disposition file. The WVU team will also create a master EMR data file that contains research ID numbers in addition to EMR data for all participants but contains no PII. The master EMR data file will contain information abstracted directly from the EMRs of participants who provide consent to share this information. AMR data will be managed as a SAS data file stored on a HIPPA compliant server maintained by WVU. The survey firm will maintain a separate consolidated master SRQ data file for each participant that contains the same research ID numbers as those used by the WVU team but contains no PII. A separate secure datafile will be maintained by the survey firm that contains only the research ID and the PII of each participant. The de-identified master EMR data file and the master SRQ data file will be merged for data processing by the WVU study team. All data analyses will be carried out with this de-identified consolidated data file jointly by the WVU and Harvard Medical School (HMS) collaborators. Access to participant data will be restricted to members of the study team listed on the IRB-approved protocol.

### Confidentiality {27}

Access to PII will be restricted to study staff identified on the IRB-approved protocol. When appropriate, information on risk for harm to self or others or significant worsening of symptomology will be reported to the patient’s primary care clinician and, in the case of acute serious suicidality, to the National Suicide Prevention Lifeline. A Certificate of Confidentiality has been obtained for this study from National Institutes of Health.

## Statistical methods

### Statistical methods for primary and secondary outcomes {20a}

The WVU analysis team will construct summary EMR variables for patients and treatment providers behind the WVU firewall and transfer these data to the survey firm via secure file transfer for linkage with the SRQ dataset behind the survey firm’s firewall. These data will be de-identified before returning to WVU and HMS for analysis. Objective 1 analyses will evaluate aggregate differences across the treatment arms. We will use logistic regression to estimate binary outcomes and report adjusted prevalence ratios with design-adjusted 95% confidence intervals (CIs). We will calculate number needed to treat (NNT) for each comparison. Generalized linear models will be used to estimate effects on continuous outcomes, making use of standard visual diagnostics to choose appropriate link functions and error structures [181]. We will report adjusted mean differences with design-adjusted 95% CIs [182].

Objective 2 analyses will evaluate HTE across the three randomized treatment arms using a special case of the super learner (SL) algorithm [183], an ensemble machine learning approach that uses cross-validation (CV) to select a weighted combination of predicted outcome scores across a collection of candidate algorithms that yields an optimal weighted combination according to a pre-specified criterion that performs at least as well as the best component algorithm. The candidate algorithms in SL can either be parametric or flexible machine learning algorithms, making SL less prone to model misspecification than traditional parametric approaches. The guarantee that SL performs at least as well as the best candidate algorithm allows a rich library of parametric and flexible candidate algorithms to be included.

In the conventional approach to estimating HTE, a model with main effects and interactions between prescriptive predictors and dummy variables for treatment indicators is estimated. Predicted values based on this model are then used to estimate the expected individual-level outcome conditional on the values of the prescriptive predictors for each patient in each treatment condition (e.g., the estimated outcomes of patient *p* under treatment arm *a*, arm *b*, and arm *c*). An estimate of the optimal treatment strategy for patient *p* is then obtained by comparing predicted values of the outcome across all treatment arms. It is important to appreciate that the accuracy of this approach requires correct specification of both the (possibly nonlinear) main effects and the (possibly complex nonlinear and higher-order) interaction terms. SL has two advantages over this conventional approach [184]. First, it requires only correct specification of the interactions. It does not require correct specification of main effects, as it directly estimates contrasts that allow the correct specification of the main effects to be circumvented. Second, unlike earlier approaches to estimating HTE that share this desirable feature [185, 186], SL uses a flexible set of component machine learning algorithms that maximize chances of capturing complex nonlinear and higher-order interactions correctly.

Objective 3 (exploratory) will examine two aspects of treatment that were not randomized: treatment with one of three broad types of ADM (SSRIs, SNRIs, bupropion) for which there is some evidence of HTE, and live psychotherapy combined with ADM rather than i-CBT with ADM. As noted earlier, 12% of West Virginia primary care MDD patients currently receive live psychotherapy. In these analyses, we will estimate a model to predict selection into each nonrandomized type of treatment as a function of baseline covariates to determine if these uncontrolled aspects of treatment are nonrandom with respect to baseline predictors. We will balance on these baseline covariates before estimating the SL model to evaluate the aggregate effects of these aspects of treatment as well as baseline predictors of HTE with respect to these aspects of treatment.

To quantify the potential value of developing a precision treatment rule for i-CBT, we will use an approach that is roughly equivalent to the calculation of NNT in aggregate analyses of treatment effects. Specifically, we will use a cross-validated targeted minimum loss-based estimator (CV-TMLE) [187] of the attained improvement of the mean outcome under a treatment selection scheme that always selects the treatment option with the best predicted outcome compared to the mean outcome under balanced randomization. This CV-TMLE yields an estimator of the attained improvement with minimal bias because it uses CV to separate the estimation of the optimal treatment strategy from the assessment of the estimated strategy’s performance and also by allowing for the incorporation of flexible estimation approaches for the regressions and conditional probabilities needed to define the attained improvement. Given that we will be evaluating the effects of expanding of treatment options rather than deciding between two alternative options (i.e., adding i-CBT to ADM rather than choosing between i-CBT and ADM as alternative monotherapies), we will evaluate a range of decision margins; that is, the expected aggregate effects on overall remission rates associated with patient decisions about adding i-CBT to ADM when individual-level increases in predicted probability of remission are in a given range. In addition, we will quantify the uncertainty in aggregate estimates in CIs.

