### Sample size {14}

We will enroll a target enrollment sample of 3360 patients who complete the baseline SRQ and are randomized across the three treatment arms (i.e., 1120 per arm). The sample was powered to detect predictors of HTE that would increase the proportional remission rate by 20% by optimally assigning individuals as opposed to randomly assigning them into three treatment groups of equal size. A much smaller sample size would be adequate to address the first study objective of evaluating the significance of differences in aggregate remission rates across the 3 treatment arms. Meta-analyses of previous trials show that the MDD symptom remission rate averages about 25% among MDD patients randomized to ADM only and 37.5% among patients randomized to combined ADM-psychotherapy [20]. Although there were no meta-analyses of remission rates for self-guided i-CBT at the time AMHI was planned, other meta-analyses showed that effects of self-guided i-CBT were significantly better than controls [30] but worse than guided i-CBT [25, 26]. We consequently assumed, for purposes of power calculations, that the patient-centered remission rate for ADM plus self-guided i-CBT in AMHI would be 31%, which is roughly midway between the extremes. Power to detect each of the 6% differences between the extremes and the middle category using a 0.05-level 1-sided test and assuming 30% loss to follow-up (which is typical of i-CBT trials) is .86, whereas power to detect the 12.5% difference between the two extremes using the same specifications is .99.

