Evaluating power to detect HTE is more complex and requires simulation. We did this by beginning with data on the observed distributions and exogenous associations among the baseline predictors in the STAR*D trial [80] and assumed that each patient was randomized across three treatment arms. We then specified a series of relatively complex nonlinear-interactive multivariate classification models for associations of these predictors with MDD remission, assuming plausible prognostic and prescriptive coefficient values that generated population distributions with the same aggregate outcome prevalence as assumed above [81]. We then modified the prescriptive coefficients to retain the aggregate remission rates while embedding HTE in the population that would result in a 20% proportional increase in the aggregate remission rate under randomization with equal allocation (i.e., from 31% to 1.2 × 31% = 37.5%). We then drew 500 pseudo-samples of different sizes from this simulated population and applied our HTE analysis method (see below) to estimate HTE in these sample data. We assumed that all the significant prognostic and prescriptive predictors were measured in the samples in addition to 20 noise predictors. Power was calculated as the proportion of replicates in which the lower bound of the 95% CI of the HTE estimate was greater than 0.0%. We also calculated proportional regret (i.e., downward bias in the estimated versus true proportional increase in remission under optimization vs. randomization). The sample size was set to yield power greater than .80 and proportional regret less than .20.

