### Methods for additional analyses (e.g., subgroup analyses) {20b}

As noted above, objective 2 is to carry out subgroup analyses that evaluate the significance of HTE and attempt to develop an ITR to make treatment assignments under balanced allocation that optimize the aggregate remission rate.

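### The rule's gain is measured against balanced randomization, so at the planned rates guided i-CBT for everyone already supplies the whole 20% HTE target without any heterogeneity

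*Protocol article*

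**What the plan says.** Protocol article, Statistical methods for primary and secondary outcomes {20a}: the attained improvement, estimated by CV-TMLE, is the average result of a rule that "always selects the treatment option with the best predicted outcome compared to the mean outcome under balanced randomization". The section promises confidence intervals and a range of decision margins for adding i-CBT. Neither this section nor any other names a single-arm policy as the comparator.

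Sample size {14}: remission "averages about 25% among MDD patients randomized to ADM only and 37.5% among patients randomized to combined ADM-psychotherapy", and self-guided i-CBT is set at 31%. Patients are "randomized across the three treatment arms (i.e., 1120 per arm"), and 30% loss is assumed for the aggregate comparisons. The HTE simulation keeps these arm rates and embeds heterogeneity worth a "20% proportional increase in the aggregate remission rate under randomization with equal allocation (i.e., from 31% to 1.2 × 31% = 37.5" percent). Power is the share of replicates in which "the lower bound of the 95% CI of the HTE estimate was greater than 0.0" percent. The sample size was chosen so that this power exceeds .80 and proportional regret stays below .20. The section adds that the aggregate comparison alone would need far fewer patients.

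Methods for additional analyses {20b}: the individualized rule is meant to "make treatment assignments under balanced allocation that optimize the aggregate remission rate".

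**The concern.** A rule free to choose any arm can beat the three-arm average simply by sending everyone to the arm that is best on average. Such a rule uses no patient information. A positive contrast with balanced randomization therefore does not show that patients differ in what works for them.

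Objective 2 sets the sample size and is meant to support a clinical decision tool. If the evidence for that tool cannot tell individualization from guided i-CBT being better on average, a rule could be adopted that adds nothing to, or even loses against, the simple policy of offering guided i-CBT to all. The planning target has the same weakness, because the printed 37.5% is also the rate assumed for the guided arm.

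**Working it through.** **Inputs** (all from Sample size {14}): arm rates p1 = .25 (ADM only), p2 = .31 (self-guided), p3 = .375 (guided); 1120 per arm; 30% loss, so n = 1120 × 0.70 = 784 evaluable per arm.

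**The plan's own figures first.** Two-proportion power, one-sided 0.05, n = 784 per arm: Φ[(|Δ| − 1.645·√(2p̄(1−p̄)/n)) / √((pa(1−pa)+pb(1−pb))/n)].
- 31% v 37.5%: .858. 25% v 31%: .842. Stated: .86.
- 25% v 37.5%: .9999. Stated: .99.

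So 784 per arm and these rates match the plan's aggregate calculation. The HTE power above .80 cannot be recomputed, because the simulation coefficients are not given.

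**Gain of guided for all with no HTE** (constant risk differences between arms):
- Balanced mean = (25 + 31 + 37.5)/3 = 31.17%.
- Gain = 37.5 − 31.17 = 6.33 points; 6.33/31.17 = 20.3%.
- Target: 1.2 × 31% = 37.2%, not the printed 37.5%; 1.2 × 31.17% = 37.4%. Guided for all reaches each of these values.

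**Chance that guided for all meets the planning criterion.** The contrast is (2/3)p3 − (1/3)p1 − (1/3)p2.
- Variance = [(4/9)(.375)(.625) + (1/9)(.31)(.69) + (1/9)(.25)(.75)]/784 = .14877/784, so SE = 1.38 points.
- z = 6.33/1.378 = 4.60; P(lower 95% bound > 0) = Φ(4.60 − 1.96) = .996. With all 1120 per arm it is .9998.

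**Dependence on guided's advantage** (my assumption: ADM only at 25%, self-guided midway, n = 784):

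| Guided rate | Gain (points) | P(lower bound > 0) |
|---|---|---|
| 31% | 3.0 | .62 |
| 33% | 4.0 | .84 |
| 35% | 5.0 | .96 |

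With three equal arms the gain is zero and the problem disappears.

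**Floor of an unconstrained optimum.** Choosing the best arm for each patient cannot do worse on average than the best arm: E[max over a of p_a(X)] ≥ max over a of E[p_a(X)] = 37.5% when arm rates are retained. A target of 37.5% is that floor, and 37.2% lies below it. On the unconstrained reading the target therefore requires no gain from individualization.

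**Equal-thirds reading.** If one third of patients must go to each arm and risk differences are constant, every assignment averages 31.17% and the gain is zero. A 20% gain then needs real heterogeneity. This fits {20b}. It may also fit the Sample size wording about three equal groups, although there the equal size may describe only the random comparator. It is not the rule defined in {20a}.

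**The case against.** The strongest reply is that the simulation may have scored a rule held to equal thirds. Adjusting prescriptive coefficients to embed a 20% gain while keeping arm rates would be pointless if the optimum were unconstrained, and it is coherent under that constraint. As an illustration on assumed inputs, independent normal individual deviations in each arm with an SD of 7.4 points give 0.846 × 7.4 = 6.3 points, about the target. This stands as a possibility. A reader might infer from the arithmetic that the stated HTE power is really power for guided's main effect. The documents do not show that, because the constraint and the coefficients are not stated.

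Second, the lower-bound criterion appears only in the power calculation. Section {20a} presents the contrast as a measure of potential value, akin to NNT, and a formal HTE test may be in the analysis plan, which is not shown. So it does not follow that the trial will declare HTE on this criterion.

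Third, the decision margins and the Objective 1 arm comparisons let a reader see guided's average advantage. They help, but neither compares the rule with a single-arm policy. Cross-validation removes overfitting from the rule's estimated value and does not change the comparator.

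Fourth, the best single arm is not the only sensible benchmark. The Discussion gives cost-effective allocation of guided i-CBT as a purpose, and a rule that matched guided for all with less coaching would score zero against it. This stands as a limit of the fix.

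Finally, the .996 belongs to the constant rule. A learned rule that strays from guided would meet the criterion less often, by an amount that depends on inputs the article does not give. Nor can the planning assumption "We assumed that all the significant prognostic and prescriptive predictors were measured in the samples in addition to 20 noise predictors" be set against the length of Table 5, since the total number of simulated predictors is not stated.

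**Conclusion.** The point holds in this form. As {20a} is written, the contrast with balanced randomization cannot separate HTE from an average advantage of guided i-CBT. At the protocol's own rates that advantage alone is worth 6.33 points (20.3%), the full planning target, and guided for all would meet the planning criterion with probability about .996. This rests on guided having roughly its assumed advantage, 30% loss, and no HTE meaning constant risk differences.

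On the unconstrained reading, the stated power above .80 is not evidence of power to detect HTE. On the equal-thirds reading it could be, but then {20a} states a different rule. The sections disagree on the estimand that justifies 3360 patients and must be reconciled. The aggregate comparisons of Objective 1 are unaffected.

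**What to change.** 1. Make Sample size {14}, {20a} and {20b} agree on whether the rule is free or held to one third per arm.
2. If it is free, base any claim of HTE or of benefit from the rule on its cross-validated value minus that of the best single arm, and keep the balanced-randomization contrast as descriptive. If it is held to equal thirds, say so in {20a}.
3. Re-run the HTE simulation for the chosen estimand with 30% loss and a no-HTE scenario at 25/31/37.5%. Add an equal-arms case, since a best-arm contrast can behave irregularly when arms tie. Restate power and regret.
4. Correct 37.5% to 37.2%, or give 31.17% as the base and 37.4% as the product.

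The cost is revised wording and a repeated simulation, with no new patients or data. The restated HTE power may be lower than now claimed. A best-arm contrast gives no credit to a rule that only saves coaching cost, so that benefit should be reported separately.
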